## Abstract

**Background:**

COPD is a highly complex disease to manage as patients show great variation in symptoms and limitations in daily life. In the last decade self-management support of COPD has been introduced as an effective method to improve quality and efficiency of care, and to reduce healthcare costs. Despite the urge to change the organisation of health care and the potential of eHealth to support this, large-scale implementation in daily practice remains behind, especially in the Netherlands.

**Methods/Design:**

We designed a multilevel study, called e-Vita, to investigate different organisational implementation methods of a self-management web portal to support and empower patients with COPD in three different primary care settings. Using a parallel cohort design, the clinical effects of the web portal will be assessed using an interrupted times series (ITS) study design and measured according to changes in health status with the Clinical COPD Questionnaire (CCQ). The different implementations and net benefits of self-management through eHealth on clinical outcomes will be evaluated from human, organisational, and technical perspectives.

**Discussion:**

To our knowledge this is the first study to combine different study designs that enable simultaneous investigation of clinical effects, as well as effects of different organisational implementation methods whilst controlling for confounding effects of the organisational characteristics. We hypothesize that an implementation with higher levels of personal assistance, and integrated in an existing care program will result in increased use of and satisfaction with the platform, thereby increasing health status and diminishing exacerbation and hospitalisation.

**Trial registration number:**

NTR4098 (31-07-2013)

## Background

Chronic obstructive pulmonary disease (COPD) represents one of the main causes of morbidity and mortality, and worldwide nearly 3 million people die from COPD every year [1]. In the Netherlands, COPD was responsible for almost 5 % of the total deaths in 2011 [2]. More than 3 million people died worldwide of COPD in 2012, which is equal to 6 % of all deaths globally that year [3]. COPD is a highly complex disease to manage as patients show great variation in symptoms and limitations in daily life. This results in a position in the top ten of most expensive diseases for respiratory disease [2]. Within the last decade self-management support of COPD has been introduced as an effective method to improve quality and efficiency of care, and to reduce healthcare costs [4–6]. It has shown to improve the level of recognition of severe exacerbations [7]. Interventions to support self-management have shown reductions in hospital admissions and fewer sick days as a result of exacerbations [8, 9]. Studies have shown that eHealth interventions are effective in stimulating self-management. Patients are better able to cope with their illness at the time and place of their choosing, allowing them to adapt their lifestyle to their condition while eHealth support also reduces medical staff consultations [10]. The deployment of eHealth applications facilitates accessibility to healthcare, which in turn enhances the patients’ understanding of their disease, sense of control, and willingness to engage in self-management [11, 12]. Although patients’ attitudes and receptiveness towards eHealth applications are promising in certain groups of age and education [13–15], large-scale adoption of eHealth in daily practice is low. Despite the urge to change the organisation of health care and the potential of eHealth to support this, large-scale implementation in daily practice remains behind on predictions, especially in the Netherlands [16].

Low adoption of eHealth in daily practice may be explained by the varying successes of eHealth programmes [17–20]-sometimes with a negative impact on quality of care and clinical effects [21]. In addition, the field of eHealth assessment is relatively new. The evaluation of eHealth research has a number of difficulties regarding evaluation methods and challenges of technology itself (usability and privacy), environmental issues that pose special problems for eHealth researchers, and logistic or administrative concerns of the selected evaluation method [11]. Therefore specific frameworks have been developed for eHealth evaluation, including evaluation of eHealth over time and based on different development stages. For example, Kaufman et al. [22] suggest that evaluation of eHealth includes specification and needs of requirements, component development, integration of components, integration in clinical setting and routine use. There are also frameworks that suggest that eHealth should be evaluated from different point of views. For example, Yusof et al. [23] suggest that human, organisational, and technological aspects and net benefits are essential components of eHealth evaluation.

eHealth shows great potential for effective COPD management. Despite the difficulties of evaluation, research of eHealth interventions is highly valuable for further adoption of eHealth in daily practice. Positive as well as negative results are needed to improve quality, utility and effectiveness, to minimize the likelihood of harm, to promote innovation, conserve resources, encourage participation, to promote confidence among users, and to promote a positive public image [24]. Therefore we designed a multilevel study to investigate implementation of a self-management web portal to support patients with COPD in primary care. As the web portal provides continuous education and contact with health care professionals, we expect it to help patients to better recognize and self-manage exacerbations in an early phase, and thereby increase health status and diminish exacerbation and hospitalisation. In this ongoing study, called e-Vita, we compare different organisational implementation methods in different primary care settings. We aim to investigate 1) the effect of self-management through eHealth on clinical outcomes and 2) the relationship between technological and organisational factors on the one hand and system use and user satisfaction on the other hand. We will therefore evaluate implementation and net benefits from human, organisational and technical perspectives (Fig. 1).

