## Methods/Design

Our primary aim is to investigate the effect of use of patient portals on clinical outcomes in primary care COPD patients (net benefits, Fig. 1). In addition, we aim to investigate the optimal organisational implementation method of the platform. Therefore we will compare different organisational implementation methods in different care settings, and evaluate their use and user satisfaction. We hypothesize that an implementation setup with greater personal support, integrated into an existing care programme will be preferred by patients and therefore be more likely to be used.

As discussed in the introduction, the evaluation of eHealth is a challenge because of the different views to evaluate from (clinical, technical, and organisational). Moreover, eHealth is not a classical clinical isolated intervention (in this case a platform) with one output (here CCQ). Instead it affects care processes, communication and patients behaviour, Finally we have a multilevel purpose to not only investigate effects but also organisational implementation methods. Therefore we made a design for a quality improvement intervention. In this study we aimed to include the importance of integration in the daily practice of primary care. Therefore we chose an implementation study [25]. We designed a method to promote the uptake of our research findings into routine primary healthcare; with this design we aim at studying the influences on healthcare professionals and patient behaviour and at evaluating the process by which effects are achieved.

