**Fig. 2 Fig2:**
[figure not shown]
Research design for the different groups and interventions of e-Vita COPD

Organisational and technical differences are depicted in Fig. 2: three different care groups and two different web portals are included. Two different methods of implementation are distinguished within group 1 and 2: one with high level of personal assistance and one with low level of personal assistance. All patients in group 1 and 2 start with a personal instruction by the primary care nurse during a regular control visit. Patients will be randomly subdivided in two groups by computer by research assistants (randomisation is computerised to prevent human influence) with high (a) and low (b) level of support. In group 1a, high level support implies home visits for patients by a research nurse who accompanies the use of the web portal. In group 2a, high level support implies telephone consultation for patients by a research nurse who accompanies use of the web portal. In group 1b and 2b low level support implies that the primary care nurse shows the patient only once how to use the web portal (the usual organisational implementation method in daily practice) without any follow-up instruction. In group 3 the web portal is offered as free use: patients will receive instructions from the web portal itself. There will be no active support from caregivers or research nurses.

The groups differ in organisation, area, use of the web portal, and integration of the portal in a COPD disease management program (Fig. 3); these characteristics are based on Dutch reports of care groups [28]:

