**Fig. 5 Fig5:**
[figure not shown]
Interventions per group

In group 1 all caregivers (GPs as well as practice nurses) will be trained to provide COPD care according to an evidence based disease management program; subsequently they implement the COPD care program in their practices under supervision of a specialized nurse. Practice nurses will receive support by a research nurse to make sure their records of COPD patients are up-to-date and to prepare consultation with their patients according to the disease management program. In addition, all practice nurses will be trained to use the web portal and to communicate with patients according to the principles of self-management.In group 2 all caregivers (GPs as well as practice nurses) will be trained shortly to ameliorate their skills in COPD care according to an evidence based disease management program that they already use. All practice nurses will be trained to use the web portal and to communicate with patients according to the principles of self-management. The training is developed and provided for by the e-Vita study group and is based on national and international guidelines.In group 3 caregivers will not receive any training. Patients will receive a brochure how to use the web portal.

The type of intervention is adopted by the care groups after thorough consideration and discussion. The e-Vita study group determined the type of platform and the level of support.

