Next, we will offer patients an online interactive care platform or web portal. The portal provides disease specific education and tips that fit their personal disease management program. In addition, the portal provides tools to report and monitor personal health goals, actions and health-related quality of life that can be shared with the patients’ own practice nurses. The portal in group 1 and 2 has better quality and more advanced possibilities for monitoring health goals with actions than the portal in group 3. The portal will be provided for a period of 15 months. Patients are informed by letter about the web portal. Patients in group 3 who agree to use the portal will receive instructions and log in information by e-mail. Patients in group 1 and 2 who agree to use the portal will be invited by their own practice nurses for intake. During intake the practice nurse defines a personal health goal together with the patient and gives instructions how and why to use the portal. Participants continue to receive regular COPD care by their GP and nurse practitioner according to the disease management program of the care group. Stable COPD patients visit their nurse practitioner yearly to check up on their disease management. The patient portal can be used by care professionals to prepare consultation or to monitor patients in-between their visits to their general practice.

Third, a subgroup of participants (1a and 2a) will receive extra support to use the portal by home visits or with instructions by telephone. During the home visit and consultation it will be checked if patients are able to log on the portal, if they understand the possibilities of the portal, and if they have started working on their personal health goal using the portal.

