This e-Vita study has several strengths. To our knowledge this is the first study to combine different study designs that enable simultaneous investigation of clinical effects, as well as effects of different organisational implementation methods whilst controlling for confounding effects of the organisational characteristics. Our hypothesis is that in well-organised primary care groups with highly skilled and motivated nurses and doctors there will be a higher use of the portal and therefore better health status. Secondly, our web portal is integrated in real life care settings and will therefore provide practical insights and knowledge of eHealth in daily practice. Third, this study adds Dutch evidence to the existing body of knowledge which is important because local political and financial factors have a major impact on successful integration in daily practice [41]. This study also includes several limitations: from a technical perspective the development of the web portal is a difficult task due to lack of broad experience in the field. The technique of the web portal and decisions made during the design phase will largely affect our outcomes but are beyond the scope and influence of our study. From a human perspective, effects through self-management imply behavioural changes. Behavioural changes require time, whereas the study period is limited to 15 months. Furthermore, patients in a primary care setting have a low burden of disease. From an organisational perspective other projects in the primary care cooperation’s can influence the speed and thoroughness of the implementation of our web portal.

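### Aim 2 promises a relationship between technological factors and portal use and satisfaction, but the only technological difference described, portal version, is completely aliased with group 3, integration, training and nurse instruction

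*Protocol article*

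**What the plan says.** The Background section of the protocol article gives two aims. The second is to investigate "the relationship between technological and organisational factors on the one hand and system use and user satisfaction on the other hand". It continues: "We will therefore evaluate implementation and net benefits from human, organisational and technical perspectives". The abstract and the opening part of Methods/Design also promise a technical view.

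The design is then described as follows.

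- **Portals** (text after Fig. 2): "three different care groups and two different web portals are included". The Intervention section allocates them, the comparison being with the one offered to group 3: "The portal in group 1 and 2 has better quality and more advanced possibilities for monitoring health goals with actions than the portal".
- **Integration** (text after Fig. 3): the portal is part of the disease management programme in groups 1 and 2, and separate from it in group 3.
- **Training** (Intervention): practice nurses in groups 1 and 2 are trained to use the portal. "In group 3 caregivers will not receive any training".
- **Start** (text after Fig. 2): every patient in groups 1 and 2 gets a personal instruction from the practice nurse. Group 3 patients rely on the portal's own instructions.
- **Randomisation** (Methods/Design): only the level of support is randomised, and only within groups 1 and 2.

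Use is recorded by log files and satisfaction by questionnaire (Adoption of the portal). The Data analysis section compares uptake across the three care groups as an organisational effect, and outcomes in groups 1+2 v group 3 as the effect of integration. It names no analysis of portal version.

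**The concern.** Aim 2 treats technology as an exposure alongside organisation. To answer that part, some technological feature must vary in a way that can be told apart from the organisational features. The one feature the article describes as varying is fixed by care group, and group 3 differs from the other two in several further respects at once.

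If use or satisfaction differs between groups 1+2 and group 3, the data support a portal explanation, an integration explanation and a training explanation equally well. The Data analysis section nevertheless gives this contrast a single label, integration. Both the technological half of aim 2 and the integration conclusion would then rest on a comparison that cannot support either one separately.

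**Working it through.** The article gives no figure to reproduce here. The question is whether the effect can be identified, so the check is on the design itself.

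**Inputs.** There are five design cells, 1a, 1b, 2a, 2b and 3 (text after Fig. 2). The Power calculation section plans 45 patients per cell: 90 + 90 + 45 = 225. The better portal therefore goes to 4 × 45 = 180 patients and the other to 45.

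**Coding of the cells from the text.**

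| Factor | 1a | 1b | 2a | 2b | 3 |
|---|---|---|---|---|---|
| Better portal | 1 | 1 | 1 | 1 | 0 |
| Integrated use | 1 | 1 | 1 | 1 | 0 |
| Caregiver training | 1 | 1 | 1 | 1 | 0 |
| Nurse instruction at start | 1 | 1 | 1 | 1 | 0 |
| High support | 1 | 0 | 1 | 0 | 0 |

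The first four rows are identical.

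**Rank of the design matrix, without and then with portal version.**

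- Intercept and integration: 2, then 2.
- Intercept, group 1 and group 2: 3, then 3.
- Intercept, group 1, group 2 and support level: 4, then 4.

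Portal version adds no information in any of these models. The rank depends on which cells exist, not on how many patients each holds, so sample size is irrelevant.

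**Correlations at 45 per cell.** Portal version with integration: 1.00. Portal version with high support: the proportions are 0.8 and 0.4, and the joint proportion is 0.4, so the correlation is (0.4 − 0.8 × 0.4) / √(0.8 × 0.2 × 0.4 × 0.6) = 0.08 / 0.196 = 0.41. Support can be separated from portal version, but only because it varies within groups 1 and 2, where the portal is the same for everyone. The randomised comparison therefore says nothing about portal version.

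**What the groups 1+2 v 3 difference estimates.** In an additive model,

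difference = portal + integration + training + nurse-led start + remaining care-group differences (including the average contribution of extra support in 1a and 2a).

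This is one equation with at least five unknown terms. As an illustration with an assumed figure, an observed difference of 20 percentage points in portal use would fit a portal effect of 0 with 20 from the other terms, a portal effect of 20 with 0 from the others, or any other split with that sum.

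**The case against.** Several objections have force.

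- **The outcomes exist.** A reader might infer that aim 2 has nothing to measure. That is not so: use and satisfaction are its outcomes, and both are collected. The gap is on the exposure side.
- **A contrast exists.** Groups 1+2 v 3 is planned and will be analysed. It is fully aliased, not absent.
- **The Discussion may not exclude technology.** Its limitations paragraph says that the portal technique and design-phase decisions "will largely affect our outcomes but are beyond the scope and influence of our study". A reader might infer that technology is thereby declared out of scope, in contradiction of aim 2. The sentence follows a remark on how hard such portals are to develop, and can fairly be read as saying that the study does not control how the portal was built. That need not rule out studying the portal as built, so the point does not rest on this sentence.
- **Other technological measures may exist.** Perceived usability can vary between patients on the same portal, and the satisfaction questionnaires are not shown. It therefore cannot be said that nothing technological can be studied, only that the one difference described cannot be isolated.
- **The aim speaks of a relationship, not an effect.** A descriptive reading is possible, but the article does not say that this is what is meant.
- **No passage says that a group difference will be attributed to technology.** This is correct. Methods/Design restates the secondary aim in organisational terms: "we aim to investigate the optimal organisational implementation method of the platform". What the article does do is attribute the contrast to integration, which the same aliasing leaves unsupported.

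A separate analysis plan could supply missing detail, but no analysis can separate factors that coincide in every cell. The aliasing and the integration label therefore stand.

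**Conclusion.** The point holds in limited form. Aim 2 names technological factors as an exposure. The only one described, portal version, coincides exactly with group 3, non-integration, no caregiver training and no nurse-led start. Its separate effect on use and satisfaction is not estimable at any sample size. The Data analysis section has no analysis of it and labels the same contrast as integration alone.

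This rests on the text alone. Figs. 1, 2, 3 and 5 are not shown. Fig. 3 lists group characteristics, so any technological difference in it would also vary only by care group. Patient-level technology measures in the unseen questionnaires cannot be excluded.

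The primary CCQ analysis within each group and the randomised support comparison in groups 1 and 2 are not affected, and the organisational half of aim 2 remains partly answerable through the latter. What changes is what may be concluded from groups 1+2 v 3.

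**What to change.** 1. In the Background section, either limit aim 2 to organisational factors, or state that its technological part is descriptive only. A workable description is use per portal function (education, goals and actions, monitoring) from the log files already planned, within the portal shared by groups 1 and 2.
2. Bring the technical-perspective wording in the abstract and in Methods/Design into line with that choice.
3. In the Data analysis section, state that any difference between groups 1+2 and group 3 is the effect of a package (portal version, integration, training, nurse-led start and care group), and will not be attributed to technology or to integration alone.

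The cost is wording, plus an optional descriptive table from existing data. No new patients, visits or measurements are needed. The downside is one claim fewer.

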**Fig. 1 Fig1:**
[figure not shown]
Model based on Yusof [22]: different aspects of eHealth evaluation

We expect to publish the first results at the end of 2016.

## Methods/Design

Our primary aim is to investigate the effect of use of patient portals on clinical outcomes in primary care COPD patients (net benefits, Fig. 1). In addition, we aim to investigate the optimal organisational implementation method of the platform. Therefore we will compare different organisational implementation methods in different care settings, and evaluate their use and user satisfaction. We hypothesize that an implementation setup with greater personal support, integrated into an existing care programme will be preferred by patients and therefore be more likely to be used.

As discussed in the introduction, the evaluation of eHealth is a challenge because of the different views to evaluate from (clinical, technical, and organisational). Moreover, eHealth is not a classical clinical isolated intervention (in this case a platform) with one output (here CCQ). Instead it affects care processes, communication and patients behaviour, Finally we have a multilevel purpose to not only investigate effects but also organisational implementation methods. Therefore we made a design for a quality improvement intervention. In this study we aimed to include the importance of integration in the daily practice of primary care. Therefore we chose an implementation study [25]. We designed a method to promote the uptake of our research findings into routine primary healthcare; with this design we aim at studying the influences on healthcare professionals and patient behaviour and at evaluating the process by which effects are achieved.

Because the most powerful studies are prospective studies, we chose a prospective parallel cohort design. We asked three primary care groups to invite their COPD patients for the e-Vita study. Because there are several differences between the groups (Fig. 3), we can not compare the COPD cohorts by combining data across three different groups. We chose for an interrupted time series (ITS) design to evaluate clinical outcomes (CCQ) within each group. In ITS studies, data are collected at multiple time points before and after an intervention in order to detect whether or not the intervention has a significantly greater effect than any underlying secular trend [26]. ITS can detect changes that are delayed or intermittent. It can also determine if the change is permanent or temporary. In addition, it allows evaluation of variables which are changing before the intervention, for instance, by comparing slopes of trend lines before and after the intervention. Finally, ITS makes it easier to control for confounding variables and regression to the mean [27]. The ITS will be performed according to guidelines of the EPOC Cochrane group [25]. Although well-conducted randomised trials provide the most reliable evidence on the effectiveness of interventions, they are not feasible for our setting of an implementation design with organisational changes in a real-life health care system within three different care groups with different demands. An advantage of an ITS design is that it allows for the statistical investigation of potential biases in the estimate of the effect of the intervention.

In addition to clinical outcomes, we also want to investigate the effect of different organisational implementation methods. Therefore we will implement the platform in group 1 and 2 using different methods. Differences will be measured using a parallel cohort design. To be certain that intervention groups will be balanced in known and unknown prognostic factors in the long run we will use randomisation within group 1 and 2. To rule out human influences we will randomise online for the level of support.

In this study we combine different study methods within one research to investigate organisational implementation methods and net benefits of eHealth interventions from human, organisational, and technical view. To do so, we created a unique study that enables us to simultaneously investigate clinical effects, as well as effects of different organisational implementation methods whilst controlling for confounding effects on an organizational level. In Fig. 2 the combined study design is shown.

